### Power calculation

A sample size estimation on data utilised data from a previous observational study performed by our group. This calculated that calculated that a TAC should provide a relative risk reduction of 67% for PTB < 30 weeks compared to TVC in this high-risk cohort of women (unpublished data). A total of 40 women in each intervention group (TAC/TVC) is required for 80% power, at 5% significance level, to show a significant difference between the two groups. This would equate to a total of 160 women in the study; 40 x group TVC vs. 40 x TAC in both groups: Group A (in pregnancy) and Group B (prior to pregnancy). The recruitment target accounts for a potential drop-out rate of 50% of Group B participants who may not have a subsequent pregnancy after randomisation; as informed by the MAVRIC trial [7].

### Trial steering committee

The role of the trial steering committee (TSC) is to provide the overall supervision of the study. The TSC will monitor the progress of the study and conduct and advise on its scientific credibility. The TSC will consider and act, as appropriate, upon the recommendations of the data monitoring committee (DMC) and ultimately carries the responsibility for deciding whether the trial needs to be stopped on the grounds of safety or efficacy. The TSC will consist of an independent chair and at least two other independent members (not involved in study recruitment and not employed by any organisation directly involved in study conduct). A representative from our dedicated preterm birth studies Patient Public Involvement group will be invited to participate. The first meeting will take place 6 months after trial start date; frequency will be decided at the first meeting (at least annually).

### Data monitoring committee

The DMC will be convened to ensure the wellbeing of study participants. The committee will periodically review study progress and outcomes as well as reports of serious adverse events (SAEs). The DMC will, if appropriate, make recommendations regarding the continuance of the study or modification of the study protocol. The DMC will meet 3 months following study commencement/recruitment of the first participant; frequency of meeting will be decided at the first meeting.

### Auditing and monitoring

The Chief Investigator will be responsible for the ongoing management of the study. The Sponsor will monitor and conduct audits on a selection of studies in its clinical research portfolio. Monitoring and auditing will be conducted in accordance with the UK Policy Framework for Health and Social Care and in accordance with the Sponsor’s monitoring and audit procedures. Protocol modifications will be communicated to relevant parties in line with UK research governance requirements. Adverse events will be reported as per regulations.

### Trial stopping rules

The ABOVE trial may be prematurely discontinued by the Sponsor, Chief Investigator or Regulatory Authority based on new safety information or for other reasons given by the DMC/TSC, regulatory authority or ethics committee concerned. If the trial is prematurely discontinued, active participants will be informed, and no further participant data will be collected. The Competent Authority and Research Ethics Committee will be informed within 15 days of the early termination of the trial.

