### Schedule of assessments

Following randomisation, the allocated procedure will be arranged. Participants in Group A will have the cerclage (TAC or TVC) inserted prior to 14 + 0 weeks’ gestation. Group B participants allocated to TAC will have the procedure placed before their next pregnancy and those allocated to TVC will have it placed during their next pregnancy before 14 + 0 weeks’ gestation. TACs are performed as an open or laparoscopic procedure under either regional or general anaesthetic, and may require an inpatient stay of up to three days. TVCs will be performed at the participant’s local maternity unit with the insertion technique and anaesthesia according to clinician’s discretion and local practices. TACs will usually remain in situ (to support any future pregnancies) while TVCs are removed at around 37 weeks’ gestation. TACs are more specialised procedures and so they may be carried out in designated specialist units, as per local practice. The timeframe between randomisation and study procedure is flexible from site to site, depending on theatre list availability, although all procedures must be carried out before the participant is 14 + 0 weeks’ pregnant.

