### Follow up procedures

There are no trial specific follow up procedures. All other pregnancy care and special preterm prevention surveillance will continue according to local clinical protocols.

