### Outcome measures

#### Primary outcome

The occurrence of mid-trimester pregnancy loss or spontaneous preterm birth before 30 weeks of gestation.

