### Data collection

Data will be collected by attending clinician or research midwives and includes: at randomisation - participant background: demographic characteristics, risk factors, obstetric history; before pregnancy trial intervention procedure (Group B – TAC); during pregnancy - trial intervention procedures (Group A - TVC or TAC, Group B – TVC); clinical care: preterm surveillance methods and test results, e.g. infection screening, cervical length measurements, caesarean section scar characteristics, predictive biomarker tests, concomitant treatments; after pregnancy - outcomes: e.g. onset of labour, gestation at delivery, infection, admission to ITU (mother) and/or neonatal unit (baby).

Data will be stored on the ABOVE Trial Database, which is hosted within the already established PCN Database (www.medscinet.net/ukpcn). This is a secure web-based platform containing standardised clinical information regarding women at high risk of sPTB. The ABOVE database’s data monitoring facility will be used to ensure data quality [10]. This function allows efficient and remote raising and answering of queries by the central and site trial teams.

The data collected will allow us to evaluate the effectiveness of the interventions on preventing poor outcomes, whether there are differences between women from different groups (demographic characteristics and risk factors) and whether treatment effects are compounded by other variables, such as intensity of preterm surveillance and concomitant treatments.

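### The early-stopping rule ends all data collection, so women already treated or pregnant when the trial stops would have no recorded outcome

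*Protocol article*

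**What the plan says.** Trial stopping rules lets the sponsor, chief investigator or regulator end the trial early "based on new safety information or for other reasons given by the DMC/TSC, regulatory authority or ethics committee concerned". The Trial steering committee section gives that committee ultimate responsibility for "deciding whether the trial needs to be stopped on the grounds of safety or efficacy". The consequence for data is stated once, without qualification: "If the trial is prematurely discontinued, active participants will be informed, and no further participant data will be collected".

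The timing comes from other sections.

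- **Schedule of assessments:** every procedure is done before 14+0 weeks, and "Group B participants allocated to TAC will have the procedure placed before their next pregnancy".
- **Primary outcome:** "The occurrence of mid-trimester pregnancy loss or spontaneous preterm birth before 30 weeks of gestation".
- **Data collection:** outcomes are gathered "after pregnancy - outcomes: e.g. onset of labour, gestation at delivery, infection, admission to ITU (mother) and/or neonatal unit (baby".
- **Follow up procedures:** the section says only this: "There are no trial specific follow up procedures. All other pregnancy care and special preterm prevention surveillance will continue according to local clinical protocols".

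**The concern.** The intervention and its outcome are separated by months. Whenever the trial stops, some women will have had the procedure, or will be pregnant under their allocation, without having reached 30 weeks. Their exposure cannot be reversed; ending collection only means that its result is not recorded. The rule applies equally to a stop for harm or for benefit, when outcomes in exposed women matter most.

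The loss is also selective. A loss at 18 weeks is known at 18 weeks, whereas freedom from the primary outcome is known only at 30 weeks. The outcomes in hand at a stop therefore contain too many failures. In Group B, women allocated to TAC may already have had abdominal surgery while those allocated to TVC are still waiting to conceive, so some of the missing follow-up falls on the more invasive arm alone.

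**Working it through.** **1. Does another section limit the rule?**

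- Follow up procedures keeps clinical care going locally. It does not keep trial data collection going.
- Auditing and monitoring has a general sentence that adverse events are reported under the regulations. It does not cover the primary outcome and does not mention reporting after a stop.
- End of study definition sets a window of six months after the last expected delivery date. It describes planned completion and does not override the stopping clause.

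None of these preserves outcomes after an early stop.

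**2. Inputs.** The article gives no figure for outcomes lost at a stop, so what follows is illustration.

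- From the article: 80 women per group with complete data, an 18-month recruitment target, a 67% relative reduction, and a possible 50% drop-out in Group B.
- Assumed: uniform accrual; Group A entry at 8 to 14 weeks; 50% of Group B conceiving within 18 months of entry at a constant rate (the article gives the 50% no time frame); TVC risk 41% (a recurrence figure in the Background), hence TAC risk 0.33 × 41% = 13.5%.
- The Power calculation states no TVC risk. At 41% versus 13.5%, with 80% power and two-sided 5%, the usual two-proportion formula gives 41 per arm (power 79.9% at 40), against the stated 40. That makes 41% a reasonable working value.

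**3. Group A, women short of 30 weeks at a stop.** Number = (80/18) × (30 − entry week)/4.35, where 4.35 is weeks per month and 80/18 = 4.44 per month.

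| Entry week | Months to 30 weeks | Women short of 30 weeks |
|---|---|---|
| 8 | 5.06 | 22.5 |
| 12 | 4.14 | 18.4 |
| 14 | 3.68 | 16.4 |

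This gives about 16 to 23 women once accrual has run for at least that many months.

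Some will already have had an event. Take the average risk (41% + 13.5%)/2 = 27.3% and spread events evenly over 14 to 30 weeks (mean 22). Women with no outcome = 4.44 × [0.727 × months to 30 weeks + 0.273 × (22 − entry week)/4.35]. This gives 20.3, 16.2 and 14.1 for entry at 8, 12 and 14 weeks.

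**4. Direction of the bias.** Take a stop at month 9 with entry at 12 weeks.

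- Successes known: 1 − 4.14/9 = 54%.
- Failures known: 1 − [(22 − 12)/4.35]/9 = 1 − 2.30/9 = 74%.
- Apparent TVC risk: 0.41 × 0.744/(0.41 × 0.744 + 0.59 × 0.540) = 49%, against a true 41%.
- Apparent TAC risk, same formula: 18%, against 13.5%.
- Apparent relative risk: 0.177/0.489 = 0.36, against 0.33.

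The absolute risks are clearly inflated. In this example the ratio moves little.

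**5. Group B at month 12.** Conception rate h = ln 2/18 = 0.0385 per month. Thirty weeks' gestation is 28 weeks after conception, or 6.44 months.

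- Conceived by month 12: 1 − (1 − e^(−12h))/(12h) = 19.9%.
- Reached 30 weeks: [5.56 − (1 − e^(−5.56h))/h]/12 = 4.6%, with 5.56 = 12 − 6.44.
- Pregnant without an outcome: 19.9% − 4.6% = 15.3%, before subtracting early events.
- Not yet pregnant: about 80%.

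**The case against.** **The harm is contingent.** It arises only if the trial stops early, and nothing in the article says how likely that is. This stands, and it limits the weight of the point without removing it.

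**Three stronger readings are tempting, and the article does not support them.**

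- *Safety follow-up or care ends for these women.* It does not. Care is local throughout, and regulatory adverse-event reporting might still capture some events. What ends is trial data.
- *Women lose long-term follow-up of a TAC.* The article says "TACs will usually remain in situ (to support any future pregnancies"), but it plans no TAC follow-up beyond the study pregnancy and neonatal outcomes. Only that planned follow-up can be lost.
- *About 95% of Group B outcomes would be lost by month 12.* Only 4.6% would have reached 30 weeks under the model above, but most of the rest are not yet pregnant. About half may never have a subsequent pregnancy by the article's own allowance, and non-conceivers are excluded from the primary analysis.

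**The bias can be avoided in analysis.** Restricting to women who would have reached 30 weeks by the stop date removes the excess of failures. This is right, so the reason for a stop would not be beyond checking. The price is precision: in the month-9 example, 54% of 40 Group A women, about 22, would remain. The restriction also recovers nothing about later maternal or neonatal outcomes in the women left out.

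**Conclusion.** The point holds as a badly fixed rule. It is an explicit instruction, not a detail left to a fuller document, and following it would discard outcomes of women already exposed.

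Its size depends on when a stop occurs. Under the stated assumptions, about 16 to 23 Group A women are short of 30 weeks at a stop (about 14 to 20 after subtracting early events), and about 15% of Group B women randomised by month 12 are pregnant without an outcome. Group B women with a TAC placed who have not conceived come on top; the article gives no basis for counting them.

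The contradiction between the rule and the outcome timing is textual and does not depend on these figures. The change should be made, but the main analysis of a trial that runs to completion is unaffected.

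**What to change.** Replace the data clause in Trial stopping rules. After early discontinuation, the already planned primary, maternal and neonatal outcomes continue to be collected from routine records for every randomised woman who has been treated or is pregnant at the stop and has not withdrawn consent. Align the information sheet and consent wording, so that permission is in place before any stop.

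One caution for analysis in Group B: a set defined as treated or pregnant retains non-pregnant TAC women but not non-pregnant TVC women. The two arms of that set should not be compared as if they were the randomised arms.

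The cost is a protocol sentence, matching consent text, and some data entry into the existing database after the stop. No visits are added, since follow-up is routine care. How procedures still pending at a stop are managed is for the sponsor and the oversight committees and is not part of this change.

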### Insurance and indemnity

The study is co-sponsored by King’s College London (KCL) and Guys and St Thomas’ NHS Foundation Trust (GSTT). The sponsors will, at all times, maintain adequate insurance in relation to the study. KCL through its own professional indemnity (Clinical Trials) and no-fault compensation and GSTT having a duty of care to patients via NHS indemnity cover, in respect of any claims arising as a result of negligence by its employees, brought by or on behalf of a study participant.

### Dissemination policy

Results of the study will be presented at national and international conferences and reported in peer reviewed journals. No patient identifiable information will be published. A lay summary of the results will be presented back to the King’s College London/ Guy’s and St Thomas’ Preterm Birth Patient and Public Involvement Group, alongside being available for participants via the study website (https://www.medscinet.net/above).

Data will not be retained for use by other researchers (in a repository). This is because it will be impossible to adequately anonymise it due to the rarity of the condition and the small number of participants that will be recruited per site.

## Discussion

The emerging evidence demonstrating the association between recurrent sPTB and MTL with in-labour CS, compounded by escalating rates of CS globally, highlights the need to develop optimal management strategies for this high-risk cohort of women. This is even more important when considering that standard interventions for the prevention of sPTB, including TVC, may be less effective in this group. It is anticipated that the RCT design of the ABOVE study will provide useful evidence concerning the effectiveness of TACs in comparison with TVCs in this cohort and the impact of placing a TAC placed prior to pregnancy compared to in early pregnancy on pregnancy outcomes. This research will inform the development of evidence-based practice.

## Data Availability

No datasets were generated or analysed during the current study.

## Abbreviations

CS: Caesarean Section
DMC: Data Monitoring Committee
EMCS: Emergency Caesarean Section
FDCS: Full Dilatation Caesarean Section
MTL: Mid Trimester Loss, pregnancy loss between 14 and 24 weeks’ gestation
PI: Principal investigator
RCT: Randomised Control Trial
REC: Research Ethics Committee
R&D: Research & Development
sPTB: Spontaneous Preterm Birth, delivery before 37 weeks completed gestation
TAC: Transabdominal Cerclage
TSC: Trial Steering Committee
TVC: Transvaginal Cerclage
